# Effects of high intensity interval training on exercise capacity in people with cystic fibrosis: study protocol for a randomised controlled trial

**DOI:** 10.1186/s13102-018-0108-2

**Published:** 2018-11-06

**Keywords:** Cystic fibrosis, Exercise, High intensity interval training

## Abstract

**Background:**

In people with cystic fibrosis (CF), higher exercise capacity is associated with better health-related quality of life (HRQoL), reduced risk of hospitalisation for a respiratory infection and survival. Therefore, optimisation of exercise capacity is an important treatment goal. The Australian and New Zealand clinical practice guidelines recommend that people with CF complete 30 to 60 min of moderate intensity aerobic exercise on most days of the week. This recommendation can be difficult to achieve by people with CF because of time constraints, and intolerable breathlessness and muscle fatigue during continuous exercise. In contrast, a low-volume, high intensity interval training (HIIT) program may be a more achievable and efficient training method to improve exercise capacity in people with CF.

**Methods:**

A randomised controlled trial will be undertaken. Forty people with CF (aged ≥15 years) will be randomly allocated, on a 1:1 ratio, to either the experimental or control group. Regardless of their group allocation, all participants will be asked to continue with their usual daily treatment for the study duration. Those in the experimental group will complete 8 weeks of thrice weekly HIIT on a cycle ergometer. Those in the control group will receive weekly contact with the investigators. The primary outcome of this study is exercise capacity. Secondary outcomes are HRQoL, exercise self-efficacy, feelings of anxiety, depression and enjoyment. These outcomes will be recorded at baseline (i.e. prior to randomisation) and following the 8-week intervention period. The study will also report other outcomes of the HIIT program (cardiovascular responses, symptom response, post-exercise muscle soreness and tolerance) and behaviour change techniques such as reinforcement, feedback and goal setting, used during the HIIT program.

**Discussion:**

This study will determine the effects of 8-weeks of supervised, low-volume HIIT, completed on a cycle ergometer on measures of exercise capacity, HRQoL, exercise self-efficacy, feelings of anxiety, depression and enjoyment. If effective, this type of training could be an attractive alternative to traditional continuous training because it may be more achievable and time efficient.

**Trial registration:**

Australian and New Zealand Clinical Trials Registry (ANZCTR):12617001271392 (04/09/2017).

## Background

Cystic fibrosis (CF) is a genetic disease which predominantly affects Caucasians [1]. Several organs are affected by CF and premature death, primarily due to respiratory failure, is inevitable [1]. Advancements in multidisciplinary care over the past 50 years have resulted in a rise in median life expectancy from 1 year in 1938 [2, 3], 10 years in 1966, 28 years in 1989 [4] to now over 40 years of age [5]. These advancements in multidisciplinary care come at the cost of a high daily treatment burden. That is, the medical, nutritional and physiotherapy regimens for people with CF are time consuming and can take up to 4 h each day [6], which need to be accommodated with the usual demands of life, such as work, study and family commitments [7].

Compared to their healthy counterparts, important markers of exercise capacity are reduced in people with CF [8, 9]. The cause of such reduction is multifactorial and includes decrements in lung function, peripheral muscle deconditioning which are both likely to contribute to severe breathlessness during exercise [8]. Additionally, people with CF may have impaired cardiac and vascular function [10–12]. In this population, higher exercise capacity, for example the peak rate of oxygen uptake (VO_2peak_), is associated with better health-related quality of life (HRQoL) [13, 14], reduced risk of hospitalisation due a respiratory infection [15] and survival [16, 17]. Given this relationship, improving exercise capacity is an important treatment goal in this population [18].

Markers of exercise capacity can be improved in people with CF by undertaking ‘traditional’ moderate intensity, continuous, aerobic exercise training [19–22]. While the optimal method of exercise training in this population requires further investigation [23], the Australian and New Zealand clinical practice guidelines recommend that people with CF complete 30 to 60 min of moderate intensity exercise on most days of the week [24]. However, in people with CF, this type of exercise training is burdensome, adding to the already high daily treatment burden, and may not be the most appropriate option due to several factors, including a ‘lack of time’ [25] and intolerable symptoms of breathlessness and muscle fatigue experienced during continuous exercise [26]. Furthermore, oxygen desaturation is more likely during moderate intensity continuous exercise [27], and this type of training may augment inflammation in this population compared to interval training [28]. An alternative training approach, such as low-volume high intensity interval training (HIIT), may be a more achievable and efficient method to optimise exercise capacity in this population [29].

High intensity interval training consists of short periods of high intensity exercise (‘work’), interrupted by periods of lower intensity exercise (‘rest’) [30]. The ‘rest’ period allows for partial recovery of symptoms such as breathlessness and muscle fatigue, and therefore offers the opportunity to optimise the training intensity achieved during the ‘work’ periods [31, 32]. In healthy adults [32] and people with chronic obstructive pulmonary disease (COPD) [33], HIIT is well tolerated and offers similar gains in exercise capacity to continuous training, with fewer symptoms of breathlessness and muscle fatigue [34, 35], and lower training time [36] or work [37] per session. Additionally, HIIT has been reported to be more enjoyable than other modes of exercise training [38]. Preliminary data suggest that HIIT is feasible in people with CF [26, 27]. However, the effectiveness of low-volume HIIT to improve exercise capacity in this population has not been investigated in a randomised controlled trial (RCT).

The primary aim of this RCT is, in people with CF aged ≥15 years, to determine the effects of an 8-week supervised low-volume HIIT program on exercise capacity (primary outcome), and HRQoL, exercise self-efficacy, feelings of anxiety, depression and enjoyment. As a secondary aim, in those allocated to receive HIIT, this study will also report on: (i) the proportion of participants who develop post-exercise quadriceps femoris muscle soreness each week during the 8-week HIIT program as well as the severity of this symptom; (ii) the participant tolerance of the 8-week supervised HIIT program; (iii) the cardiorespiratory and symptom responses elicited during the HIIT sessions throughout the 8-week program and; (iv) the behaviour change techniques (BCTs) employed throughout the program. If the HIIT program is shown to be effective at improving exercise capacity, the implementation of such a time efficient program will result in a lower treatment burden, compared to undertaking moderate intensity continuous exercise and therefore may be more readily incorporated into the daily routine of people with CF.

## Methods

This is a prospective, single-blinded RCT. The study has been approved by the relevant ethics committees and has been registered with the Australian and New Zealand Clinical Trials Registry (ANZCTR) (12617001271392, 04/09/2017). Participant recruitment will commence in September 2017. The study will be reported in accordance with the Consolidated Standards of Reporting Trials (CONSORT) statement [39]. The study flow diagram is presented in Fig. 1.

**Fig. 1 Fig1:**
[figure not shown]
Study design flow diagram

### Recruitment and consent

Potential participants will be identified and recruited from scheduled outpatient clinic appointments at the adult (Sir Charles Gairdner Hospital [SCGH]) and children’s (Perth Children’s Hospital ([PCH]) CF centres. Potential participants will be provided with an information sheet summarising the study and will receive a phone call within 48 h of their clinic visit to discuss their willingness to participate. At the beginning of the first study visit, written informed consent will be obtained from participants or assent if the participant is under 18 years of age.

#### Inclusion and exclusion criteria

Males and females with CF will be invited to participate in this study if they: (i) are aged ≥15 years and; (ii) have a body mass index (BMI) > 16 kg/m^2^. Exclusion criteria will comprise: (i) current or recent (within the previous 4 weeks) exacerbation of CF which required oral or intravenous antibiotics; (ii) a co-morbid condition that would impact on the ability to undertake a maximal incremental exercise capacity test; (iii) poorly controlled diabetes as deemed by their treating endocrinologist; (iv) previous lung transplant or current listing for lung transplantation; (v) participation in exercise at a moderate intensity two or more times per week for the previous 3 months and; (vi) the inability to provide written informed consent due to a cognitive impairment or being unable to understand English. If a potential participant has cystic fibrosis-related diabetes, they will be included pending approval from the treating endocrinologist, irrespective of the treatment they are on.

### Randomisation and allocation concealment

Participants will be randomly allocated, on a 1:1 ratio, to either the experimental or control group. Concealment of the allocation sequence will be ensured by using a central randomisation service (the National Health and Medical Research Council randomisation service). A minimisation algorithm will be used to stratify for site of recruitment (i.e. SCGH or PCH), spirometry (i.e. mild [FEV_1_ ≥ 70% predicted], moderate [FEV_1_ 40 to 69% predicted] or severe [FEV_1_ ≤ 39% predicted]) and the use (or not) of Ivacaftor, which is a medication that improves lung function, weight, HRQoL and reduces the rate of exacerbation [40].

### Assessment period

Both prior to randomisation (i.e.baseline) and following the intervention period (i.e. follow-up), participants will complete assessments over two non-consecutive days; assessment day one and assessment day two. Each assessment visit will last 1.5 h, and both visits will be completed within 2 weeks. During both the baseline and follow-up assessments, descriptive variables will be recorded related to age, gender, height, weight, genotype and spirometry (Medgraphics USB Spirometer, MCG Diagnostics, Minnesota, USA). Measures related to the primary aim will be collected in both groups during the baseline and follow-up assessment. This will comprise exercise capacity, HRQoL, exercise self-efficacy, feelings of anxiety, depression and enjoyment. The follow-up assessments of these outcomes will be completed by an assessor who is blinded to group allocation. Measures related to the secondary aim will be collected in the experimental group only and will comprise post-exercise muscle soreness (measured weekly), tolerance (measured at every HIIT session) and cardiorespiratory and symptom responses to HIIT (measured at week 1, week 4 and week 8 of the HIIT program) will be measured throughout the 8-week period. Details of these measurements are provided below.

#### Assessment day one

On the first assessment day each participant will complete a ramp-based cycle ergometry test on an electronically-braked cycle ergometer (Ergoselect 100; Ergoline, Bitz, Germany). The test will commence with 1 min of rest, followed by 1 min of unloaded cycling. Thereafter, a ‘continuous ramp’ protocol will be used to progressively increase the work rate until the participant is unable to continue due to intolerable symptoms (i.e. symptom limitation). The magnitude of change in work rate will be individualised based on the participant’s age and pre-existing level of fitness (as subjectively reported by the participant), with the aim of achieving symptom limitation in 8 to 12 min [41]. Throughout the test, participants will be asked to cycle at a cadence of 60 rpm. Breath by breath measurements will be collected of minute ventilation, breathing pattern, rate of oxygen consumption (VO_2_) and rate of expired carbon dioxide production (VCO_2_) (Medgraphics CardioO_2_; Medical Graphics Corporation). Measures of heart rate (HR) and oxygen saturation (SpO_2_) will be continuously monitored and recorded using a 12 lead electrocardiogram and an ear probe attached to a pulse oximeter (Ohmeda Biox 3700e ear probe, Colorado, USA), respectively. Blood pressure will be measured every 2 min using an automated blood pressure (BP) machine (Tango M2; Suntech, North Carolina, USA) with a BP cuff connected to the participants’ right arm. Measures of breathlessness and muscle fatigue will be recorded each minute using a modified Borg scale [42]. The peak rate of oxygen uptake (VO_2peak_) will be defined as the average VO_2_ during the final 30 s of the test [43].

Following completion of the ramp-based cycle ergometry test, the participants will be asked to complete two questionnaires: (i) the Cystic Fibrosis Questionnaire- Revised (CFQ-R) [44, 45] which takes approximately 15 min to complete and is a valid and reliable questionnaire for use in people with CF [44, 45], and; (ii) the Barriers Self-efficacy Scale (BARSE) [46], which takes approximately 5 min to complete and is a valid and reliable tool in healthy people [46].

#### Assessment day two

On a separate, non-consecutive day, the constant work rate test will be performed in order to establish time to symptom limitation (T_lim_) (primary outcome). This test will be conducted using identical equipment and measurements as described for the ramp-based cycle-ergometry test. Participants will be asked to complete a 1-min warm-up of unloaded cycling after which the work rate will be increased to 80% of the W_max_ [48]. An intensity of 80% of the W_max_ has been chosen as this has been demonstrated to be feasible in people with CF [48]. In addition, at this cycling intensity, more than half of people with chronic respiratory disease (CF or COPD) achieve a T_lim_ of between 8 and 11 min; a test duration which is most responsive to change following the intervention period [49, 50]. During the baseline assessment, if a participant does not demonstrate signs of symptom limitation at 10 min, then the test will be terminated and, following a seated rest of 30 min, the test will be repeated at a higher intensity [43, 50]. During the follow-up assessment, the constant work rate test will be completed at the highest work rate used during the baseline assessment. In the follow-up assessment, the constant work rate test will be terminated at 20 min for participants who do not reach symptom limitation earlier and T_lim_ will be recorded as 20 min.

Following completion of the constant work rate exercise test, participants will be asked to complete three questionnaires; (i) the Alfred Wellness Score for CF (AweScore-CF) [51], which takes approximately 2 min to complete and is a reliable tool for use in people with CF [51]; (ii) the Hospital Anxiety and Depression Scale (HADS) [52], which takes approximately 10 min to complete, is a valid, reliable and responsive measure and has been widely used in people with CF [52], and; (iii) the Physical Activity Enjoyment Scale (PACES), which is a valid and reliable tool previously used in healthy people and takes approximately 5 min to complete [53].

### Intervention period

Regardless of group allocation, throughout the duration of the study, participants will continue usual care. This includes medication, nutritional support, airway clearance regimens and attendance at a multidisciplinary outpatient CF clinic, which occur quarterly, or more frequently if clinically indicated. In both groups, usual care for each participant will be recorded weekly throughout the intervention period. To do so, participants will be asked if there have been any changes to their treatment in the preceding week.

#### Experimental group

Participants allocated to the experimental group will be asked to complete an 8-week cycling-based HIIT program. Each training session will involve a 2-min active ‘warm up’ at 15 to 20 W, followed by a 30-s ‘work’ phase and 30-s ‘rest’ period, repeated six times. The work to rest periods will be followed by a 2-min active ‘cool down’ period at 15 to 20 W. Therefore, the total training time per session, inclusive of rest periods, will be 10 min. Each session will be supervised by a physiotherapist who is trained in the management of people with CF. To minimise the onset of post-exercise muscle soreness and optimise adherence, the training program will commence with a ‘lead in’ phase which will involve only two sessions of HIIT in weeks 1 and 2. Thereafter, between weeks 3 and 8, HIIT will be undertaken three times a week (i.e. total 22 sessions over 8 weeks). The training intensity will be prescribed using measurements of maximum work rate (W_max_) achieved during the ramp-based cycle ergometry test completed during the baseline assessments. Specifically, the first training session will be prescribed at 60% of W_max_, with the goal of achieving a training intensity equal to 80% of W_max_ during the fourth training session (i.e. the end of week 2). Thereafter, training intensity will be increased as rapidly as symptoms of breathlessness and muscle fatigue permit. Training will be completed at one of two sites, with the participant permitted to choose the site that is most convenient for them. The model of exercise bike used for the HIIT sessions will be identical across all training sites (Orbit Eco Generator Interval Bike OEB2002, Perth, Australia). Only a single participant will be permitted to use the exercise room on any day, with stringent hand hygiene and cleaning procedures adhered to at all times to reduce the risk of cross contamination between participants [54]. The intervention will be conducted and reported in accordance with the TIDieR checklist [55] and CERT guidelines [56, 57].

If a participant in the experimental group reports the onset of symptoms indicative of an exacerbation of CF (i.e. increased sputum volume, changes in the characteristics of sputum, blood present in the sputum, increased cough, pain from coughing, new wheeze or increased wheeze, new or increased chest tightness, shortness of breath or difficulty breathing, increased fatigue or lethargy, fever, loss of appetite or weight, sinus pain or tenderness) [58], they will be referred to their respective CF team for medical review. If an exacerbation is diagnosed by the treating CF team, the participant will be invited to continue participating in HIIT sessions once deemed to be medically stable by a CF clinician. Medical stability has been defined as being afebrile, having resting BP, HR and SpO_2_ within limits of the participants’ baseline values and/or deemed stable by the treating CF clinician. In the event of missed attendance to HIIT sessions, the training program will be extended by a maximum of 2 weeks so that the participant will have 10 weeks to complete the 22 HIIT sessions.

#### Measurements related to the secondary aim (collected in the experimental group only)

##### Post-exercise muscle soreness

Participants in the experimental group will be asked if they experienced any post-exercise quadriceps femoris muscle soreness whilst completing a ‘sit to stand’ 24 h following the first training session of each week. Those who report experiencing post-exercise muscle soreness will be asked to rate its severity using a Visual Analogue Scale (VAS) [59].

##### Tolerance

The level of participant attendance and completion of the HIIT sessions will be recorded throughout the 8-week period. Oxygen saturation (SpO_2_) at rest and nadir SpO_2_ will be recorded during each training session. Adverse events will be monitored throughout the HIIT program. These will be categorised as minor, if they are transient and self-limiting events (i.e. breathlessness without significant oxygen desaturation [< 4% from the participant’s pre-exercise SpO_2_], muscle or general fatigue) or major events if they require the participant to cease training during any given session or necessitate medical assistance (i.e. breathlessness with significant oxygen desaturation [≥ 4% from the participants pre-exercise SpO_2_], pain, vasovagal events or haemoptysis).

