#### Control group

Participants allocated to the control group will be contacted once a week by a physiotherapist to discuss changes to their symptoms, healthcare utilisation and participation in exercise over the preceding week. Participants will be allowed to choose the way in which this contact is made; phone calls, texts or emails. If a participant allocated to the control group reports any symptoms that are suggestive of an exacerbation, they will be referred to the CF team for medical review.

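### Adverse events are recorded only in the HIIT arm, and no exacerbation or harm outcome is ascertained alike in both arms, so harms that also arise from background CF cannot be compared by arm as planned

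*Protocol article*

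**What the plan says.** All references are to the protocol article.

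- **Where adverse events are collected.** They are defined in one place, the Tolerance section: "Adverse events will be monitored throughout the HIIT program". The parent heading reads "Measurements related to the secondary aim (collected in the experimental group only", and the Assessment period section repeats the limit: "Measures related to the secondary aim will be collected in the experimental group only".
- **What counts.** Minor events are transient and self-limiting, with breathlessness short of the desaturation limit and muscle or general fatigue as examples. Events are graded as "major events if they require the participant to cease training during any given session or necessitate medical assistance", with haemoptysis among the examples.
- **Exacerbations.** In both arms, suggestive symptoms lead to referral. For the HIIT arm the Experimental group section gives a detailed symptom list and then says "they will be referred to their respective CF team for medical review". The Control group section says that if a control "reports any symptoms that are suggestive of an exacerbation, they will be referred to the CF team for medical review". Exacerbation is neither a named adverse event category nor a named outcome.
- **What is gathered in controls.** They are "contacted once a week by a physiotherapist to discuss changes to their symptoms, healthcare utilisation and participation in exercise over the preceding week", by phone, text or email as they choose. The Intervention period section adds a weekly record of usual care, including any treatment change, in both groups.
- **Analysis.** Under Statistical analyses, tolerance is summarised descriptively. The list of outcomes for the mixed models is introduced as examples and contains no harm or exacerbation outcome.

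**The concern.** A count of adverse events in one arm of a randomised trial can be interpreted only if the events could not have happened without the intervention. That is true of desaturation during a training session. It is not true of haemoptysis, fatigue, an event needing medical assistance or an exacerbation, all of which can arise from CF itself. For these, the randomised control group supplies the background rate, and the plan does not record adverse events there.

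The same occurrence can therefore be treated differently by arm. Blood in the sputum in a HIIT participant may be classed as an adverse event; in a control it prompts referral and no adverse event record is specified. At stake is the harms half of the trial's report. The Discussion expects the study to be able to influence practice, and readers will want to know whether such events were more, less or equally common with HIIT.

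**Working it through.** **1. The plan's own figure.** The only calculation given is the sample size for T_lim. Inputs: difference 100 s, SD 99 s, α = 0.05 (two-sided assumed), power 0.80. Then n per group = 2 × (1.96 + 0.84)² × (99/100)² ≈ 15.4, rounded up to 16, so 32 in total; 32/(1 − 0.20) = 40. The figure reproduces. It concerns T_lim and has no bearing on harms, beyond fixing the trial at about 20 per arm.

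**2. Which events need a control count.**

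| Event in the Tolerance section | Can it occur in a control? | Counterpart in the exacerbation symptom list (Experimental group) |
|---|---|---|
| Desaturation from the pre-exercise value | No, tied to a session | – |
| Stopping a training session | No, tied to a session | – |
| General fatigue | Yes | Increased fatigue or lethargy |
| Haemoptysis | Yes | Blood in the sputum |
| Event needing medical assistance | Yes | Any listed symptom that leads to medical review |

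Post-exercise soreness has its own section and is also tied to training. One-arm collection is reasonable for session-bound events. It is not adequate for the last three rows.

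**3. Opportunities to detect an event.**
- HIIT arm: 2 sessions × 2 weeks + 3 sessions × 6 weeks = 22 supervised sessions.
- Control arm: 1 contact × 8 weeks = 8 contacts, possibly by text or email.
- Ratio: 22/8 = 2.75.
- The HIIT programme may run to 10 weeks if sessions are missed. No matching extension is stated for controls, so the observation periods may also differ.

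**4. What a by-arm report would deliver.** The documents give no event risks, so those below are assumptions. With the same risk p in each arm, the half-width of the 95% CI for the risk difference is 1.96 × √(2p(1 − p)/n):

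| Assumed risk | n = 20 per arm | n = 16 per arm |
|---|---|---|
| 10% | ±18.6 points | ±20.8 points |
| 20% | ±24.8 points | ±27.7 points |
| 30% | ±28.4 points | ±31.8 points |
| 40% | ±30.4 points | ±33.9 points |

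Power at 20 per arm for a 20-point difference:

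| Assumed risks | Normal approximation | Fisher exact |
|---|---|---|
| 10% v 30% | 35% | 24% |
| 20% v 40% | 28% | 19% |
| 30% v 50% | 25% | 16% |

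**5. An illustration (assumed counts, Wald intervals).** Suppose 4/20 HIIT participants have an event.
- Against 1/20 controls: difference 0.20 − 0.05 = +15 points; SE = √(0.20 × 0.80/20 + 0.05 × 0.95/20) = 0.102; 95% CI about −5 to +35.
- Against 5/20 controls: difference 0.20 − 0.25 = −5 points; SE = √(0.20 × 0.80/20 + 0.25 × 0.75/20) = 0.132; 95% CI about −31 to +21.

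The intervals overlap heavily, but each is an estimate. Without a comparable control count there is none, at any sample size.

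**The case against.** The strongest reply is that the trial already gathers most of what is needed. Treatment changes, which would include a new antibiotic course, are recorded weekly in both groups. Controls are asked about symptoms and healthcare use, and suspected exacerbations go to the CF team in both arms. **This stands against a stronger reading.** A reader might infer that the trial cannot say anything about whether HIIT changes exacerbations. The documents do not support that: treated exacerbations could be compared after the fact. Such a comparison would be unplanned and would carry the unequal detection shown above.

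Four further points on that side:

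- **The Tolerance section is about tolerance of training, and much of it is session-bound.** This stands for those events and is why they should remain HIIT-only. It does not cover haemoptysis, general fatigue or medical assistance.
- **A recommendation for HIIT would not rest on efficacy alone.** Correct. Attendance, completion, nadir SpO2, graded adverse events and soreness are all collected. What is missing is the comparator.
- **Claims about exacerbations can go too far.** Nothing in the article says that they are the main competing event or that they reduce T_lim, and the programme extension follows missed sessions for any reason. The point does not depend on these claims.
- **An article condenses the full protocol.** This would excuse silence about forms or safety tables. It does not excuse an explicit statement, made twice, that these measures are taken in one arm only.

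Finally, a common form does not equalise contact, and 40 participants cannot test harms. Both are true, and both limit what the fix can achieve.

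**Conclusion.** The point holds as a limit on what can be reported about harms. Adverse event recording is confined to the HIIT arm by an express rule, and no harm or exacerbation outcome is defined for both arms with the same ascertainment. Events that also arise from background CF therefore cannot be compared by arm as planned. The primary outcome and its analysis are unaffected.

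The gain from correcting this is modest: a by-arm estimate in place of a one-arm count, with an interval of roughly ±20 to ±30 points at 20 per arm and slightly wider at 16. These widths rest on assumed risks of 10% to 40%. It is a cheap improvement that should be made, not a flaw that undermines the trial.

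**What to change.** 1. At the weekly contact, complete one identical form in both arms: the symptom list in the Experimental group section, any diagnosed exacerbation, any antibiotic course, healthcare use, and adverse events outside training sessions. Ask the same questions at the same weekly interval, and do not fill the HIIT form from remarks made at other sessions.
2. Fix the same observation period for both arms. For example, count events over the same number of weeks from randomisation and show any during the HIIT extension separately.
3. Name as a between-group safety outcome the number of participants with at least one event, by arm, with a risk difference and 95% CI. State that this is descriptive estimation, with no hypothesis test.
4. Keep desaturation during sessions, stopped sessions and post-exercise soreness as HIIT-only tolerance data, and label them so.
5. Acknowledge in the report that supervised sessions still give the HIIT arm more chances to mention symptoms.

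No change to referral or clinical care is involved. The cost is a short form and slightly more data entry at contacts that already take place; the downside is wide intervals that need to be reported with restraint.
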